## Methods/Design

### Study population and study design

The Mesh Ablator versus Cryoballoon Pulmonary Vein Ablation of Symptomatic Paroxysmal Atrial Fibrillation (MACPAF) study is designed as a prospective randomized single center study conducted by the Department of Cardiology and Pneumology (Charité, CBF), the Center for Stroke Research Berlin and the Department of Neurology (Charité, CBF). The study has been approved by the local Ethics Committee (EA4/087/08) in February 2009. Randomization started in April 2009. Study entry and storage of data require subsequent consent by the patient. The inclusion and exclusion criteria are summarized in Table 1. Before undergoing LACA, patients receive an implantable device (Reveal XT^®^, Medtronic, Inc.) able to record the AF burden for at least 2 years. Within 24 h before LACA, all patients undergo transesophageal echocardiography (for exclusion of atrial thrombi), a brain MRI as well as a neuro(psycho)logical examination. A repeat brain MRI and neuro(psycho)logical examination will be performed within 48 h after the procedure. Patients will be randomized 1:1 for the cryoenergy device (Arctic Front^®^) or the newest device using conventional radiofrequency (HD Mesh ablator^®^). Before PV ablation, a CT image will be performed and segmented by CARTO Merge^® ^(Biosense Webster, Inc.) for visualization of PV anatomy. The LACA procedure will be performed by first introducing a ring shaped decapolar catheter via a single transseptal puncture. Afterwards, this catheter will be exchanged for the cryoballoon catheter or the mesh ablator, respectively. Finally, PV conduction will be re-evaluated by the decapolar catheter. In case of remaining PV conduction, the ablation procedure will be continued until isolation of all PVs is achieved. After transseptal puncture, heparin will be given to assure an activated clotting time of >300 s. Follow-ups will take place at 1, 3, 6, 9 and 12 months after LACA, including data acquisition from the Reveal XT^® ^or a 5-day-holter-ECG, respectively. Brain MRI and neuro(psycho)logical examination will be repeated after 6 months. The patient will be put on oral anticoagulation (INR 2-3) for at least 6 months after LACA to improve comparability of the results. The end of study is expected for late 2011.

**Table 1 T1:** MACPAF: Inclusion and exclusion criteria.

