### Aims and objectives

The primary objective of MACPAF is the efficacy of PV isolation, defined by achieving an exit block for all PVs per patient. We hypothesize that the cryoballoon catheter is more effective compared to the mesh ablator catheter in this regard. This is the only objective, which can not be assessed in a blinded fashion for the used ablation catheter. The secondary objective is the detection of LACA-associated (silent) cerebral thromboembolism by brain MRI and by neuro(psycho)logical examination. Further objectives are the determination of the AF recurrence rate after LACA using an implantable device, the detection of non-neurological major complications after LACA and the detection of (silent) cerebral thromboembolism within 6 months after LACA.

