### Sample size calculation and Statistical analysis

The primary endpoint for a patient is achieved when all four pulmonary veins are isolated. We hypothesize that corresponding to this primary endpoint the Arctic Front^®^ catheter is superior to the HD Mesh Ablator^®^ catheter. The null hypothesis of equal proportions of successful outcomes for both methods will be tested by the two-sided Fisher's exact test at significance level 0.05. Assuming a proportion of 75% successful ablations for the HD Mesh Ablation^®^ catheter, sample sizes of 54 for both treatment groups achieve 80% power to detect a 20% greater proportion of successes for the Arctic Front^®^ catheter. This corresponds to a proportion of 95% successful ablations for the Arctic Front^®^ catheter - a relative improvement of 27% for the Arctic Front^®^ catheter in comparison to the HD Mesh Ablator^®^ catheter.

An intention-to-treat analysis will be used to analyze treatment differences concerning predefined outcome measures. Treatment allocation will be done by gender-stratified randomization. For all outcome variables descriptive statistics will be collected. For quantitative traits, we will compute absolute and relative frequencies. In the case of continuous or quasi-continuous variables with nearly symmetric distribution, we will compute arithmetic mean, standard deviation, minimal and maximal values, otherwise median, quartiles, minimal and maximal values. Fisher's exact test will be used to compare proportions for dichotomous outcomes between independent groups or to test independency of two dichotomous traits within a population. Hypotheses about proportions for dichotomous outcomes within a single group (one sample analysis) will be tested by the binomial test. Assuming equal shaped distributions in the two treatment groups for at least ordinal scaled outcome variables group specific location parameters will be compared by the t-test or the Mann-Whitney test, respectively, depending on normality or non-normality of the distribution. Analysis regarding time to first AF-recurrence: Defining 'no observed AF-recurrence between 3 months after LACA and the end of follow-up' as 'survival', survival functions will be estimated by the Kaplan-Meier method. The null hypothesis of equal survival curves for the two treatment groups will be tested by the Log-Rank test.

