### Neuropsychological examination

The neuropsychological assessment was designed to assess important cognitive domains and includes the following tests: Trail Making Test A and B (information processing and divided attention), the Stroop Test, the Category and Letter Fluency Test (all three assessing different aspects of executive functions) [22], the subtest 3 from the German Leistungsprüfsystem (reasoning) [23], a German version of the Rey Auditory Verbal Learning Test [24], the digit-span forward and backward test from the Wechsler Memory Scale - Revised [22] (verbal short-term and working memory), the German Mehrfachwahl-Wortschatz-Intelligenztest (MWT-A Test; educational level) [25] as well as the Rey-Osterrieth Complex Figure Test (visuo-spatial skills and visual memory) [22].

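### The only between-arm tests named for continuous and ordinal outcomes are unadjusted, and the plan does not say how the pre-ablation neuropsychological score enters the comparison

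*Protocol article*

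**What the plan says.** All references are to the protocol article.

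- **Method.** Sample size calculation and Statistical analysis gives one rule for every outcome that is at least ordinal. It opens "Assuming equal shaped distributions in the two treatment groups for at least ordinal scaled outcome variables" and continues "group specific location parameters will be compared by the t-test or the Mann-Whitney test, respectively, depending on normality or non-normality". The rule names no outcome, time point or covariate, and does not say whether the variable is a post-ablation value or a change. The same section states that randomisation is stratified by gender.
- **Measurements.** Under Study population and study design, within 24 h before LACA "all patients undergo transesophageal echocardiography (for exclusion of atrial thrombi), a brain MRI as well as a neuro(psycho)logical examination". Afterwards, "A repeat brain MRI and neuro(psycho)logical examination will be performed within 48 h after the procedure", and "Brain MRI and neuro(psycho)logical examination will be repeated after 6 months".
- **Instruments.** Under Neuropsychological examination: "The neuropsychological assessment was designed to assess important cognitive domains and includes the following tests". The list covers attention, executive function, reasoning, verbal and visual memory, and yields continuous or ordinal scores.
- **Role.** Under Aims and objectives: "The secondary objective is the detection of LACA-associated (silent) cerebral thromboembolism by brain MRI and by neuro(psycho)logical examination".

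**The concern.** The battery is given before and after the procedure so that procedure-related change can be told apart from differences between people that were there already. The stated two-sample tests do not say how they use that pairing.

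Two things follow if post-ablation scores are compared directly. Stable differences between patients stay in the error term, and a chance difference between the arms at baseline carries over into the estimated catheter effect. If change scores are compared, the baseline is used, but with a fixed weight of one. That is inefficient when the correlation is moderate or low.

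The rule also leaves open which variable is analysed and lets observed normality pick the test, for many subtests at two time points. The Discussion concedes that the number of patients might not allow correction for multiple testing, so an analysis fixed in advance matters more here.

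**Working it through.** **The plan's own figure.** The only power stated is for the primary endpoint: 80% with 54 per arm, 75% against 95%, two-sided Fisher's exact test at 0.05. Exact enumeration over the two binomials gives 79.1% at 54 per arm and 80.1% at 55, so the figure is reproduced to within a point. It is not touched by what follows. No power is stated for the neuropsychological scores.

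**Inputs.**
- From the article: 54 per arm, 1:1 allocation. The two-sided 0.05 level is stated for the primary test and carried over here.
- Assumed: a true difference of 0.4 SD, equal SD before and after, complete data, and a correlation r between baseline and follow-up varied from 0.3 to 0.8.

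**Variance of the arm difference, relative to a post-only comparison.**
- Post-only: 1
- Change from baseline: 2(1 − r)
- ANCOVA on baseline: 1 − r²

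ANCOVA is never worse than post-only, because 1 − r² ≤ 1. It is never worse than change, because (1 − r²) / [2(1 − r)] = (1 + r)/2 ≤ 1. A change score beats post-only only when 2(1 − r) < 1, that is when r > 0.5.

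**Power.** The standard error of a mean difference in SD units is √(2/54) = 0.192, so the post-only noncentrality is 0.4/0.192 = 2.08. For the other two analyses this is divided by the square root of the relative variance. At r = 0.7 ANCOVA has 2.08/√0.51 = 2.91 and change has 2.08/√0.60 = 2.68. The noncentral t distribution then gives:

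| r | ANCOVA relative variance | Change relative variance | Power, post-only | Power, change | Power, ANCOVA |
|---|---|---|---|---|---|
| 0.3 | 0.91 | 1.40 | 54% | 41% | 58% |
| 0.5 | 0.75 | 1.00 | 54% | 54% | 66% |
| 0.6 | 0.64 | 0.80 | 54% | 63% | 73% |
| 0.7 | 0.51 | 0.60 | 54% | 76% | 82% |
| 0.8 | 0.36 | 0.40 | 54% | 90% | 93% |

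In sample-size terms, at r = 0.7 the trial's 54 per arm under ANCOVA are worth 54/0.51 ≈ 106 per arm in a post-only comparison. Any further gain from adding gender is not counted.

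**Chance imbalance.** The baseline mean difference also has a standard error of 0.192 SD. At r = 0.7 an imbalance of one standard error shifts a post-only contrast by 0.7 × 0.192 ≈ 0.13 SD, about a third of the assumed 0.4 SD effect. ANCOVA corrects for this shift.

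**The case against.** The strongest reply is that the article never says post-ablation scores are compared without the baseline. The rule is generic, and a t-test or Mann-Whitney test on change from baseline fits it equally well. The design even points that way: the later examination is called a repeat, and the objective concerns effects attributable to LACA. This stands. A reader might infer that the baseline is ignored, but the text does not support that. On the change-score reading the gain from ANCOVA shrinks to 3 percentage points at r = 0.8 (93% against 90%).

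It also stands that r and the 0.4 SD effect are assumptions, that the gain is slight over post-only at r = 0.3 (58% against 54%), and that an unadjusted comparison in a randomised trial is unbiased and keeps its type I error. The named tests are less efficient, not invalid.

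A last reply is that a condensed article may leave such detail to a full protocol or analysis plan that is not shown. This stands only in part. A fuller document may well settle how baseline enters. But the article does commit to a specific class of tests for these outcomes, and a more precise one is available from data already scheduled. The point is about that stated choice, and it holds whichever variable was meant.

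**Conclusion.** The point holds as a low-cost improvement to the analysis of a secondary objective. The article names only unadjusted two-sample tests, chosen by normality, and does not fix how the pre-LACA score is used. ANCOVA is at least as precise as both readings at every r.

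Its size is conditional. With 54 per arm and an assumed 0.4 SD difference, the gain in power over post-only scores is about 19 points at r = 0.6 (73% − 54%) and 39 at r = 0.8 (93% − 54%). Over change scores it is about 10 points at r = 0.6 (73% − 63%) and 3 at r = 0.8 (93% − 90%).

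Two stronger statements are tempting but not supported. One is that a large part of the precision is being wasted, which needs both a post-only analysis and r of about 0.6 or more, and the article gives neither. The other is that procedure-related cognitive effects are very unlikely to be detected. Even the post-only test has 54% power for 0.4 SD. The primary endpoint and the sample size are unaffected.

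**What to change.** For each neuropsychological score, at 48 h and at 6 months, state that the arms are compared by ANCOVA with the pre-LACA score and gender (the stratification factor) as covariates. For tests expected to be skewed, such as timed ones, name in advance a rank-based or transformed scale, and drop the choice of test by observed normality. Report the adjusted difference with its confidence interval.

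The cost is wording in the analysis section. The baseline examination is already planned for every patient, so no visit, test or patient is added. If a fuller analysis plan already specifies this, the generic rule in the article should be brought into line with it. The change should be fixed before scores are compared by arm.

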### MRI analysis

MRI examination is performed if the patient is able to give informed consent. Using a 3T MR scanner (Tim Trio; Siemens AG, Erlangen, Germany) the following sequences will be done 24 hours before as well as 24-48 hours after the ablation procedure: T2*-weighted imaging to screen for intracranial hemorrhage; diffusion-weighted magnetic resonance imaging (DWI) to assess cerebral infarction; Fluid-attenuated inverse recovery (FLAIR) to estimate microangiopathic lesions load and to investigate the age of recent lesions; time-of-flight MR-Angiography (TOF MRA) to detect vessel stenosis or occlusion. Six month after LACA a third measurement without TOF MRA will be performed to assess the incidence of (silent) strokes by time. For sequence parameters see [19]. Blinded MRI reading will be done by a board certified neuroradiologist ([name]).

### Neurological examination

The National Institute of Health Stroke Scale (NIHSS) is a validated instrument used in many clinical trials to assess neurological deficits of stroke patients [20]. The NIHSS displays the subjects' consciousness, the ability to move limbs, the sensorium, speech, vision and eye movements. The modified Rankin Scale (mRS) is used to quantify the persisting handicap after stroke [21].

### Neuropsychological examination

The neuropsychological assessment was designed to assess important cognitive domains and includes the following tests: Trail Making Test A and B (information processing and divided attention), the Stroop Test, the Category and Letter Fluency Test (all three assessing different aspects of executive functions) [22], the subtest 3 from the German Leistungsprüfsystem (reasoning) [23], a German version of the Rey Auditory Verbal Learning Test [24], the digit-span forward and backward test from the Wechsler Memory Scale - Revised [22] (verbal short-term and working memory), the German Mehrfachwahl-Wortschatz-Intelligenztest (MWT-A Test; educational level) [25] as well as the Rey-Osterrieth Complex Figure Test (visuo-spatial skills and visual memory) [22].

## Discussion

The pulmonary vein (PV) ablation in patients with symptomatic paroxysmal atrial fibrillation (AF) has received increasing attention over the last years and is now a well-established therapeutic approach to limit symptomatic paroxysmal AF [6,7]. The use of novel catheter techniques gives reasons to expect better safety and efficacy, but there is little clinical evidence so far [16,17]. Performing MACPAF, we hypothesize that the cryoenergy device (Arctic Front^®^) is superior to the balloon based device using radiofrequency (HD Mesh ablator^®^) with regard to efficacy and safety. Efficacy of LACA will be assessed by achieving a complete PV isolation as an acute effect, and by a lack of AF recurrence after a blanking period of three months (long-term efficacy), evaluated by an implantable device able to detect AF.

Focusing on the safety of LACA, the use of diffusion-weighted magnetic resonance imaging will precisely detect (silent) cerebral infarction, as recently demonstrated using a 1.5T MRI [15]. The use of a 3T MRI enables a higher resolution, improving the significance of stroke detection, while the detection of cerebral hemorrhage, chronic lesions and brain vessel occlusion is at least equal to 1.5T MRI [26]. Therefore, we expect a higher rate of silent strokes than the reported 10-11.3% [14,15]. Furthermore, the MACPAF study will demonstrate if the incidence of clinically silent or clinically evident strokes differs within the tested ablation systems. Moreover, a retrospective analysis of MACPAF might identify LACA procedure-independent risk factors, hopefully reducing LACA-associated stroke rate according to optimized technical conditions and patient selection. Using an implantable device for AF detection and a follow-up MRI after 6 months, we will be able to correlate the rate of (silent) strokes with the AF burden in patients on oral anticoagulation.

According to a http://www.clinicaltrial.org search, the MACPAF study meets highest technical standards. To eliminate potential conflicts of interest, this is an investigator-initiated clinical trial.

Nevertheless, the MACPAF study has its strengths and limitations. Firstly, using two balloon based ablation systems, our results are not transferable to other LACA procedures. Secondly, focusing on paroxysmal AF, we are unable to address questions regarding persistent AF. Thirdly, the assessment of the predefined endpoints is blinded but the LACA procedure itself can not be done in a blinded fashion. Fourth, the limited number of patients might not allow correction for multiple testing. Fifth, according to the study design, a placebo-arm is not intended. The lack of a placebo arm is justified as ablation is a clinically indicated procedure and thus withholding any ablation would be unethical. Prospective multicenter studies will be needed to clarify these important issues.

Taken together, MACPAF is a prospective randomized single-center trial to compare the efficacy and safety of LACA for paroxysmal AF using two balloon based catheter techniques. Results from MACPAF will provide important information helping cardiologists and neurologists to better counsel AF-patients concerning risks and benefits of LACA. Doing MACPAF, we hope to make a significant contribution to the evaluation of the LACA-associated (silent) stroke risk, setting the stage for stroke-risk reduction by improved technical conditions and appropriate patient selection.

## List of abbreviations

AF: atrial fibrillation; LACA: left atrial catheter ablation; MRI: magnetic resonance imaging; MACPAF: Mesh Ablator versus Cryoballoon Pulmonary Vein Ablation of Symptomatic Paroxysmal Atrial Fibrillation Study; PV: pulmonary veins.
